### Inclusion criteria

Eligible patients are patients with M0-MIBC, treated with radical cystectomy and ePLND with ≥1 of the following characteristics:pathological (p)T3-MIBC with presence of lymphovascular invasion on pathological examinationpT4 -MIBC<10 lymph nodes removedpresence of pathological positive lymph nodespositive surgical margins

andWHO performance state 0–2Age ≥ 18 years oldWilling and able to provide a signed informed consent

### Exclusion criteria

Presence of distant metastasis at time of inclusionPrevious pelvic irradiationPresence of any psychological, familial, sociological or geographical condition potentially hampering compliance with the study protocol and follow-up schedulePresence of a second primary tumour other than accidental finding of completely removed prostate cancer, non-melanoma skin tumour or tumour diagnosed ≥5 years ago

### Evaluation and inclusion

A flow chart presenting the different steps from inclusion until treatment is presented in Fig. 1. EBRT should start during week 6–12 after radical cystectomy.

**Fig. 1 Fig1:**
[figure not shown]
Overview of study flow chart. Abbreviations: p: pathological; EBRT: external beam radiotherapy; RC: radical cystectomy

### Intervention

A ^18^F–FDG-PET-CT is recommended but not obligatory within 4–10 weeks after radical cystectomy to rule out distant metastases.

All patients receive a planning CT on week 5–10 after radical cystectomy. Planning CT is performed in supine position with 3 mm CT slice thickness from the lung top till mid femur.

The target volume comprises the pelvic lymph node areas at risk in all cases. This stems from the observation that most recurrences are in the pelvic sidewall region so that the central pelvis, and the cystectomy bed in particular, might reasonably be spared treatment unless margins are involved [8, 11]. The lymph node regions at risk are the lymph nodes located along the common, internal and external iliac artery, the lymph nodes in the obturator fossa and the presacral nodes. Suspicious lymph nodes on ^18^F–FDG-PET-CT imaging are delineated separately. All delineated lymph node regions at risk are then summed to a structure named as Lnn. The clinical target volume (CTV)_Lnn is then created using an isotropic expansion of 2 mm around the Lnn. The planning target volume (PTV)_Lnn is created using a 5 mm margin around the CTN_Lnn.

The bladder bed is only included in the radiation field if there is a positive surgical margin [8, 14]. Pre cystectomy imaging as well as information obtained from the surgical report and anatomopathological evaluation is used for delineation of the bladder bed.

A median dose of 50 Gy is prescribed to the pelvic lymph nodes ± bladder bed and is delivered in 25 fractions, 5 times a week. A simultaneous integrated boost up to 70 Gy (corresponding to a normalised iso-effective dose of 74 Gy in 2 Gy fractions calculated with an α/β of 10 [35]) to the positive lymph nodes, detected on (^18^F–FDG-PET-)CT, is prescribed. VMAT is used. The treatment is delivered on a linear accelerator using 6–18 MV photons and multileaf collimation [23, 24]. Patient positioning during treatment is controlled by daily cone beam CT.

### Follow up

Patients are followed weekly during therapy, 1 month after therapy and 3- monthly thereafter. After the end of radiotherapy and at each follow up visit a standard blood control (including sedimentation, erythrocytes, leucocytes (including formula), thrombocytes, creatinine, electrolytes, liver parameters, alkaline phosphatase) is performed. In asymptomatic patients imaging (CT thorax/abdomen/pelvis) will be performed 3–6-monthly after the end of radiotherapy during the first year and 6-monthly thereafter up to a period of 5 years and yearly thereafter or until progression.

### Statistical analysis

#### Sample size

We plan to perform a multicentric prospective phase 2 study in which 76 patients will be enrolled. With this sample size there is 95% likelihood that no more than 25% ± 10% [21] of the patients will develop severe toxicity (i.e. grade ≥ 3 toxicity requiring hospitalization and/or surgical re-intervention) after adjuvant radiotherapy. This number takes into account 5% percentage of missing data.

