Little is known about the timing of EBRT combined with radical cystectomy in MIBC. Preoperative EBRT can prevent intra-operative seeding of tumor cells and sterilizes microscopic extensions in the perivesical tissues. However, a meta-analysis of six randomized trials showed no clear benefit for preoperative irradiation [18]. Adjuvant EBRT also has the advantage of dealing with microscopic cells along with a better identification of patients who are really at increased risk of developing local recurrence based on histological information of the primary tumor. Already two decennia ago, adjuvant EBRT was tested in a prospective randomized trial and resulted in a 20% increase in 5-year disease free survival (DFS) [19, 20]. These results were supported by a non-randomized controlled Radiation Therapy Oncology Group trial [21]. Also in the era of modern surgery it is suggested that adjuvant radiotherapy improves outcome. Shariat et al. found that, although a limited number of patients, adjuvant radiotherapy was independently associated with lower disease recurrence (HR: 3.3, 95% CI: 2.2–4.9; *p* < 0.001) and improved disease specific survival (HR: 2.4, 95% CI: 1.6–3.7; *p* < 0.001) while in the same study the impact of adjuvant chemotherapy on similar outcomes was less clear [6]. Despite those encouraging results, severe intestinal toxicity rates hampered the enthusiasm to use adjuvant EBRT, in fact till now [19, 21]. However, the technology that was used in the above-mentioned trials is outdated and conclusions concerning toxicity do not apply to the current technologies such as intensity-modulated radiotherapy (IMRT) and volumetric arc therapy (VMAT) and image guided radiotherapy [22–24]. Therefore, it is reasonable and even desirable to reconsider the use of adjuvant EBRT in properly selected MIBC patients.

This “proper” selection should be based on clinical, pathological, radiological and biological predictors for local and locoregional failure. Well-known clinical and pathological predictors are T-stage, lymph node status [6, 25], presence of lymphovascular invasion [6] and surgical margin status [10].

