## Discussion

For patients with MIBC neo-adjuvant chemotherapy and radical surgery is standard of care [3]. Unfortunately the outcome remains poor for high-risk MIBC patients and the overall survival hasn’t improved significantly over the past years. Further efforts to improve the outcome of these patients are therefore mandatory. Previous trials showed that adjuvant radiotherapy can improve DFS at the cost of severe toxicity [9–20]. The latter limited the enthusiasm to propose adjuvant radiotherapy to patients with high-risk MIBC. In the last decade, major technological advancements in radiotherapy delivery have been realized, resulting in a better coverage of the target volume while sparing more normal tissue (mainly small bowel) and in a more precise delivery of radiation. VMAT is such a technique that can significantly reduce late toxicity [23, 24]. Furthermore, better insights in the pattern of local relapse, based on large surgical data [8–10], enable us to tailor and restrict the radiation field to the area that is at highest risk of developing recurrence. Based on these observations there is a renewed interest in reevaluating the place of adjuvant radiotherapy in those MIBC patients who are at increased risk of developing disease recurrence [36]. The aim of this prospective phase 2 trial is to support the hypothesis that with modern radiotherapy toxicity of adjuvant radiotherapy after radical cystectomy is acceptable.

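### The sample-size sentence claims a 95% likelihood of limited toxicity, but 76 patients only fix the width of a confidence interval around an assumed 25%

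*Protocol article*

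**What the plan says.** All statements are in the protocol article.

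- **Sample size:** the size of the single-arm trial is 76 ("We plan to perform a multicentric prospective phase 2 study in which 76 patients will be enrolled"). Its only justification is the sentence "With this sample size there is 95% likelihood that no more than 25% ± 10% [21] of the patients will develop severe toxicity". Severe toxicity is specified there as "grade ≥ 3 toxicity requiring hospitalization and/or surgical re-intervention". An allowance is added: "This number takes into account 5% percentage of missing data".
- **Data analysis:** the primary endpoint is acute toxicity up to 3 months after radiotherapy. No limit, interval or number of events is attached to it.
- **Discussion:** the aim is to support the hypothesis that "with modern radiotherapy toxicity of adjuvant radiotherapy after radical cystectomy is acceptable".

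**The concern.** The sentence has two faults.

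1. It presents a probability about the toxicity outcome as something that the sample size delivers. A sample size controls how precisely a rate is estimated. It cannot make a low rate likely.
2. *No more than* sets an upper bound, whereas *± 10%* describes a two-sided interval. In "no more than 25% ± 10% [21] of the patients will develop severe toxicity" the two are joined. The reader cannot tell whether the bound is 25% or 35%, or whether it applies to the observed rate or to a confidence limit.

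The sentence is the article's sole basis for the sample size, and it concerns the primary safety endpoint. Taken literally, it offers an assurance about serious harm that the design does not provide.

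**Working it through.** **Inputs (Sample size section).** Assumed rate p = 0.25; margin d = 0.10; level 95%, read as two-sided, z = 1.96; missing data 5%; stated n = 76.

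**Step 1: reproduce 76.** The Wald precision formula for one proportion gives

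n = z² p(1−p) / d² = 1.96² × 0.25 × 0.75 / 0.10² = 72.03.

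Allowing for 5% missing data, 72.03 / 0.95 = 75.8, so 76. (72.03 × 1.05 = 75.6 also gives 76. Rounding up to 73 before inflating gives 77.)

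The other designs tried do not give 76:

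- One-sided 95% precision gives 51, or 54 with missing data.
- A one-sample normal-approximation test with 5% type I error and 80% power needs 133 (one-sided) or 169 (two-sided) for 35% against 25%.
- The same test for 25% against 15% needs 103 or 133.

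So 76 is a confidence-interval width calculation.

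**Step 2: what 76 delivers.** Evaluable patients: 76 × 0.95 = 72.2, taken as 72.

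- Wald half-width at 25%: 1.96 × √(0.25 × 0.75 / 72) = 0.100, so 15% to 35%.
- Exact (Clopper–Pearson) 95% interval for 18/72: 15.5% to 36.6%.
- If all 76 are evaluable, the half-width is 9.7 points and the exact interval for 19/76 is 15.8% to 36.3%.

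**Step 3: test the likelihood claim.** Exact binomial probabilities with n = 72. An observed rate of at most 25% means at most 18 events. At most 35% means at most 25 events (0.35 × 72 = 25.2). Between 15% and 35% means 11 to 25 events (0.15 × 72 = 10.8).

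| True rate | P(observed ≤25%) | P(observed ≤35%) | P(observed 15–35%) |
|---|---|---|---|
| 15% | 99.1% | >99.9% | 52.4% |
| 20% | 88.4% | 99.9% | 87.6% |
| 25% | 56.3% | 97.6% | 96.0% |
| 30% | 21.5% | 84.2% | 84.1% |
| 35% | 4.6% | 53.4% | 53.4% |
| 40% | 0.6% | 21.5% | 21.5% |

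In every column the probability changes widely with the true rate, so no single 95% belongs to the sample size. The entry that corresponds to the plan's own inputs is 96.0%: an observed rate within 10 points of 25% when the true rate is exactly 25%. That is the precision statement of step 2 again, not an upper bound on toxicity.

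**Step 4: what the ambiguity is worth.** Suppose, for illustration, that a one-sided 95% exact upper limit had to lie below the bound. A bound of 35% allows at most 18/72 events; a bound of 25% allows at most 11/72. The two readings are 7 events apart.

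**The case against.** The strongest reply is that this is loose wording for a standard precision calculation. The stated inputs produce the stated number. Every sample-size statement is conditional on a planning value, and at 25% the chance of observing 15% to 35% is indeed 96.0%. Even the one-sided reading with a bound of 35% exceeds 95% if the true rate is 25% or lower. All of this stands: 76 needs no correction. But the sentence does not state the condition, and without it the claim is wrong. That the exact upper limit is 36.6% rather than 35% reflects the choice of interval method and is not an error.

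A reader might infer more than the document supports:

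- **That the trial tolerates 35% toxicity.** The article never names 35% as acceptable. It arises only by adding the margin to 25%. The 53% at a true rate of 35% is therefore not a false-acceptance rate of the plan, since no acceptance rule is stated.
- **That the trial lacks a success criterion and cannot answer its question.** The article shows none, but it condenses a full protocol, and that protocol or the SAP may hold one. An estimate with an interval of about ±10 points can also inform the stated aim.
- **That 25% is a wrong benchmark because it is cited to reference 21.** The Background does group that trial among those where "severe intestinal toxicity rates hampered the enthusiasm to use adjuvant EBRT, in fact till now [19, 21]", and it calls the technology outdated. Using an older figure as a level not to be exceeded is compatible with that view. What the reference reports cannot be checked here.

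**Conclusion.** The sentence is wrong as written and should be corrected; the sample size is right. With 76 enrolled and about 72 evaluable, the plan obtains a two-sided 95% interval of about ±10 points around an observed 25%. It does not obtain a 95% likelihood that severe toxicity stays at or below 25% or 35%. At a bound of 35% the probability for the observed rate is 98%, 84% and 53% at true rates of 25%, 30% and 35%. At a bound of 25% it is 56%, 21% and 5%.

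These figures assume independent patients, a common toxicity rate and 72 evaluable. With all 76 evaluable they barely move: for the 35% bound, 97%, 82% and 50%. The conclusion is about what the article claims for its sample size. It does not extend to the enrolment figure, the choice of 25%, or the absence of a decision rule from documents not shown.

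**What to change.** **Correction.** Replace the sentence with, for example:

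> Assuming a severe-toxicity rate of 25%, about 72 evaluable of 76 enrolled patients give a two-sided 95% confidence interval of about ±10 percentage points (exact 95% CI for 18/72: 15.5% to 36.6%).

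Drop the claim of a 95% likelihood of staying below a limit, and with it the combination of an upper bound and a two-sided margin. The cost is wording only: no change of sample size, conduct or analysis. The stated property becomes less reassuring, but it is one that the design has.

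**Suggestion, subject to the full protocol or SAP.** If the trial is to conclude that toxicity is acceptable, base this on the upper confidence limit against a limit that the sponsor names in advance, and report the operating characteristics. For illustration only: a one-sided 95% exact upper limit below 35% requires at most 18/72 events. This is met with probability 4.6% at a true rate of 35%, 56% at 25% and 88% at 20%. Such a rule adds no patients, but it has only a moderate chance of success at the planning rate of 25%, and this should be stated openly. Write it in terms of the confidence limit rather than a fixed count, because the count shifts with the number evaluable (at most 17 for 70–71, 18 for 72–74, 19 for 75–76).

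### The sample-size sentence presents a confidence-interval half-width of 10 points as a 95% probability that severe toxicity stays under a limit; the number 76 is right, its stated meaning is not

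*Protocol article*

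**What the plan says.** The Sample size paragraph, under Statistical analysis in the protocol article, sets the number: "We plan to perform a multicentric prospective phase 2 study in which 76 patients will be enrolled". It then says what that number achieves: "With this sample size there is 95% likelihood that no more than 25% ± 10% [21] of the patients will develop severe toxicity". Severe toxicity is defined there as "grade ≥ 3 toxicity requiring hospitalization and/or surgical re-intervention", and the allowance for missing data is given as "This number takes into account 5% percentage of missing data".

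The paragraph does not mention a confidence interval. It also does not say that the 95% depends on any assumed or observed rate. The Discussion gives the trial's aim as "to support the hypothesis that with modern radiotherapy toxicity of adjuvant radiotherapy after radical cystectomy is acceptable".

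**The concern.** Read literally, the sentence says that enrolling 76 patients makes it 95% probable that the proportion with severe toxicity will not exceed a limit. No sample size can do that. The number of patients determines how precisely a rate is estimated. Whether the rate stays under a ceiling depends on the true rate, which the trial is there to estimate.

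The wording also joins an upper limit (no more than) to a symmetric margin (±10%), so the reader cannot tell whether the ceiling is 25% or 35%.

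The article gives no other statistical property for its toxicity assessment. Severe intestinal toxicity is the reason it gives, in the Background, for the past reluctance to use adjuvant radiotherapy. An ethics committee or a later report could therefore cite this sentence as a 95% safety assurance that the design does not provide.

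**Working it through.** **Inputs, all from the Sample size paragraph:** rate 25%, margin 10 percentage points, level 95%, missing data 5%, 76 patients enrolled.

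**Step 1. Reproduce 76.** Precision of one proportion, normal approximation, two-sided 95%:

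n = z² × p × (1 − p) / d² = 1.96² × 0.25 × 0.75 / 0.10² = 72.03

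Allowing for 5% missing: 72.03 / 0.95 = 75.8, so 76. (Rounding 72.03 up to 73 first gives 73 / 0.95 = 76.8, so 77, a difference of one patient.)

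**Step 2. Check that other readings do not give 76.**
- One-sided 95% margin: 1.645² × 0.25 × 0.75 / 0.10² = 50.7; 51 / 0.95 = 53.7, so 54.
- One-sample test of 35% against 25%, one-sided 5%, 80% power: [(1.645 × √(0.35 × 0.65) + 0.842 × √(0.25 × 0.75)) / 0.10]² = 132 evaluable.

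Of the readings tried, only the two-sided interval width gives the stated number.

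**Step 3. What 76 patients provide.** Evaluable: 76 × 0.95 = 72.2, about 72. If 18 of 72 (25%) have the event, the two-sided 95% interval is:
- normal approximation: 25% ± 1.96 × √(0.25 × 0.75 / 72) = 25% ± 10.0 points, 15.0% to 35.0%;
- Wilson: 16.4% to 36.1%;
- exact (Clopper-Pearson): 15.5% to 36.6%.

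With all 76 evaluable, the half-width by normal approximation is 9.7 points.

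**Step 4. The probability of staying at or below a ceiling.** Exact binomial, 72 evaluable. An observed rate of at most 35% means at most 25 events (0.35 × 72 = 25.2). A rate of at most 25% means at most 18 events.

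| True rate | P(observed ≤ 35%) | P(observed ≤ 25%) |
|---|---|---|
| 20% | 99.9% | 88% |
| 25% | 98% | 56% |
| 30% | 84% | 21% |
| 35% | 53% | 5% |
| 40% | 21% | 0.6% |

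With all 76 evaluable, P(observed ≤ 35%) is 97% at a true rate of 25% and 50% at 35%, so the pattern is the same.

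For the probability to equal 95%, the true rate would have to be about 26% to 27% if the ceiling is 35%, or about 18% if it is 25%. The 95% is therefore a consequence of the rate one assumes, and the choice of ceiling matters.

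**Step 5. The most favourable reading.** If the true rate is exactly 25%, the observed rate falls between 15% and 35% (11 to 25 of 72) with probability 96.0%; with 76 evaluable it is 95.4%.

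**The case against.** The strongest defence is that this is a planning statement with an unspoken condition. Under the 25% that the sentence itself prints, the observed rate lies within ±10 points with probability about 96%, and at or below 35% with probability about 98%. On that view the sentence is clumsy, and the number behind it is sound. One could also read it as an expected rate of at most 25%, estimated to within 10 points.

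Much of this stands. The arithmetic is right, no patient number or planned analysis changes, and the two halves of the sentence are ambiguous without being irreconcilable. The defence does not rescue the wording. The condition is not stated, and it assumes the quantity that the trial is meant to measure. An upper-limit phrase also turns a symmetric precision statement into a ceiling.

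A reader might go further, in four ways that the document does not support:
- **That the true assurance is 56% and not 95%.** This takes 25% as the ceiling and ignores the printed ±10%. With the margin included, the matching figure at a true 25% is 96% to 98%.
- **That the trial is too small because it may fail to exclude 35%.** The article never calls 35% unacceptable; it is only the upper end of 25% ± 10%. Any cut-off on event counts would be the reader's own, and it shifts with the method: an upper limit below 35% allows at most 16 of 72 events with a two-sided 95% exact interval, but 18 of 72 with a one-sided 95% exact bound.
- **That the Discussion rests its claim of acceptable toxicity on this sentence.** The Discussion states an aim. It does not cite the sample-size paragraph or any of its figures.
- **That the exact upper limit of 36.6%, against 35%, is an error.** It is only the difference between exact and approximate intervals.

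**Conclusion.** The sentence is wrong as written. The error is one of interpretation: 76 is correct as the number that gives a two-sided 95% interval of about ±10 points when the observed rate is 25%. It does not give an unconditional 95% assurance of any upper limit. With 72 evaluable patients, the chance of observing at most 35% falls from 98% at a true rate of 25% to 84%, 53% and 21% at 30%, 35% and 40%. The statement is nearly true only under the unstated condition that the true rate is 25%.

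This rests on 72 evaluable patients, derived from the stated 5% missing data, and on independent binomial outcomes. The source cited for the 25% was not available and is not relied on. An unseen analysis plan would not change the conclusion, because the point concerns what the article affirms and not something it leaves out.

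**What to change.** Remove the probability claim and its upper-limit phrase, and put in its place:

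*76 patients (about 72 evaluable after 5% missing data) give a two-sided 95% confidence interval of about ±10 percentage points (exact 15.5% to 36.6%) if the observed severe-toxicity rate is 25%.*

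No decision threshold is proposed here. If the sponsor wants to make an upper-limit claim, it should be written as a rule on the confidence limit, naming the limit and whether the bound is one- or two-sided, with the probability of meeting it at plausible true rates.

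The cost is one reworded sentence. No patients are added and no endpoint or treatment changes. The stated assurance becomes less favourable, because the sentence will no longer read as a safety guarantee.

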### Data analysis

The primary endpoint is acute toxicity defined as any toxicity from start of adjuvant EBRT up to 3 months following adjuvant EBRT.

The incidence of late toxicity will be recorded. Actuarial risk estimates for developing late toxicity will be calculated using Kaplan Meier analysis.

QOL will be evaluated pre-radiotherapy, at the end of radiotherapy and 1 month after radiotherapy. Thereafter a 3 monthly evaluation will be performed during the first year and 6-monthly up to 2 years after radiotherapy.

DFS, bladder cancer specific survival and overall survival will also be calculated using Kaplan Meier actuarial analysis. Survival times are defined from the date of radical cystectomy until an event or last follow up.

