## Background

Muscle invasive bladder cancer (MIBC) is the ninth most frequently diagnosed cancer and ranks 13th in terms of causes of death worldwide [1]. The incidence of bladder cancer increases steadily with age. Due to improved life expectancy, the number of patients diagnosed with MIBC is expected to increase in the future.

A radical cystectomy combined with an extended pelvic lymph node dissection (ePLND) is considered to be the treatment of choice. Cisplatin-based neo-adjuvant chemotherapy improves survival outcomes and is recommended for patients with cT2-T4a N0–1 M0 MIBC [2, 3]. Despite this multimodality treatment the outcome did not altered significantly over the last 30 years [4] and remains poor with 5-years overall survival rates ranging between 50 [5] and 60% [6] to 65% [7]. For patients with ≥pT3 MIBC the 5-year overall survival even drops to as low as 22% [8]. Others have reported somewhat better results with a 5-year bladder cancer specific survival of 31 and 48% for T4 and T3 MIBC patients respectively [6].

Besides the high rate of systemic recurrences, loco-regional control is equally important. Approximately 30% of patients with ≥pT3 tumors develop a pelvic recurrence [8–10]. For instance, in a contemporary monocentric analysis from a high-volume, tertiary center focusing on 334 pT3–4 pN0–1 MIBC patients, 31% of patients developed a pelvic recurrence, 34% of which had loco-regional only failure. Chemotherapy, whether immediately postoperative (adjuvant) or delayed at time of recurrence, might improve the outcome of patients with MIBC as was suggested in a recent meta-analysis [11]. Unfortunately, these results are based on very inhomogeneous data. The conclusions of this meta-analysis are not considered to be robust and it remains unclear which patients really benefit from it [12]. Generally, neo-adjuvant chemotherapy is preferred, which does not interfere with this trial. Currently, there are also several trials already running or being initiated looking at the use of adjuvant immunotherapy with MIBC. While this approach looks promising, eventual adjuvant immunotherapy does not exclude adjuvant radiotherapy. In fact, there might be an additional benefit in the combination [13].

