### Objectives

*Primary endpoint*
○ Acute toxicity defined as toxicity occurring during or within 3 months following adjuvant EBRT and scored by:▪ Acute Radiation Therapy Oncology Group (RTOG) small and large intestine toxicity [28] and Common toxicity criteria version 4.0 (CTC v4.0) [29]▪ Acute RTOG [28] and CTC v4.0 [29] bladder toxicity for patients with a neobladder only

*Secondary endpoints*
○ Quality of life (QOL) scoring using the EORTC QLQ-C30 supplemented with QLQ-BLM30 prior to, at the end and 1 month after adjuvant EBRT, then 3-monthly during the first year and 6-monthly up to 2 years.○ Assessment of quality-adjusted-life-years with the EuroQol classification system (EQ-5D) [30]. A written consent to use this system was obtained from the EuroQol Group Foundation.○ Assessment of erectile function using the International Index of Erectile Function (IIEF) questionnaire [31] in males and sexual function in females [32].○ Assessment of voiding pattern using the International prostate Symptom Score (I-PSS) [33] and International Consultation on Incontinence Modular Questionnaire Urinary Incontinence (ICIQ-UI) Short Form [34] for patients with a neobladder.○ Late toxicity due to radiotherapy will be scored using RTOG [28] and CTC v4.0 [29] scoring systems. Late toxicity is defined as toxicity lasting more than 3 months after cessation of adjuvant EBRT, or starting more than 3 months after the end of adjuvant radiotherapy.○ Local control rate defined as absence of recurrence within the pelvis. This will be evaluated on pelvic CT scans performed on predefined time-points (see below) or in case of suspicion of recurrence.○ DFS defined as survival without evidence of disease recurrence (neither local recurrence, recurrence in lymph nodes or distant metastasis) and is calculated from date of radical cystectomy till diagnosis of local, regional or distant recurrence on CT scan at predefined time-points or in case of suspicion of recurrence.○ Bladder cancer specific survival calculated from date of radical cystectomy till death due to MIBC.○ Overall survival calculated from date of radical cystectomy till death of any cause.○ Serum samples and urine samples after cystectomy will be collected and stored in a biobank. Biomarkers will be evaluated on all samples in duplicate and correlated with DFS and bladder cancer specific survival.

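### Late toxicity is to be estimated by Kaplan-Meier with death outside the event, which overstates the actual risk by about 1.2 to 1.9 fold at 5 years over the cited survival figures

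*Protocol article*

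**What the plan says.** The Data analysis section makes two statements on late toxicity. First, "The incidence of late toxicity will be recorded". Second, "Actuarial risk estimates for developing late toxicity will be calculated using Kaplan Meier analysis". No competing-risk method is named.

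The definition is under Objectives, secondary endpoints: "Late toxicity is defined as toxicity lasting more than 3 months after cessation of adjuvant EBRT", or toxicity that begins after that time. Death is not part of the event.

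The only rule on how follow-up ends is written for the survival endpoints: "Survival times are defined from the date of radical cystectomy until an event or last follow up". The article does not say how a death without toxicity is handled in the late-toxicity analysis.

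The Background gives the expected mortality. Five-year overall survival in muscle-invasive disease is put at 50% to 65%. For more advanced disease it says "For patients with ≥pT3 MIBC the 5-year overall survival even drops to as low as 22" per cent, and then "Others have reported somewhat better results with a 5-year bladder cancer specific survival of 31 and 48% for T4 and T3 MIBC patients".

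**The concern.** A patient who has died can no longer develop late toxicity. When toxicity is the only event, a Kaplan-Meier analysis censors that patient and so treats the person as if toxicity could still occur later, at the same rate as in the survivors. The result is the risk in a hypothetical cohort in which nobody dies. It is always at least as large as the proportion of treated patients who will experience late toxicity, and the gap widens with mortality and with length of follow-up.

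Both conditions apply here. Eligibility selects high-risk patients, and imaging follow-up runs 6-monthly to 5 years and yearly thereafter. According to the Discussion, the trial is meant to support the view that toxicity of modern adjuvant radiotherapy is acceptable. For that purpose a reader will take the late figure as the share of patients harmed, and 1-KM does not estimate that share.

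**Working it through.** **The plan's own figures.** The article states no late-toxicity rate, so there is none to reproduce. Its one computed design figure, the 76 patients, reproduces: 1.96² × 0.25 × 0.75 / 0.10² = 72.03, and 72.03 / 0.95 = 75.8, rounded up to 76. The Kaplan-Meier choice plays no part in it.

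**Inputs**
- Five-year survival S₅ (Background): 22% (overall survival, ≥pT3, one series); 31% and 48% (bladder cancer specific, T4 and T3); 50% and 65% (overall survival, ends of the range for muscle-invasive disease). Using the two cancer-specific figures as if they were overall survival understates mortality slightly.
- Late-toxicity hazard λt: assumed 5% per year, with 3% and 10% as the range.
- Hazards constant from the end of radiotherapy (assumed).

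**Formulas**
- Death hazard: λd = −ln(S₅)/5
- Kaplan-Meier risk: 1-KM = 1 − exp(−λt·T)
- Cumulative incidence with death competing: CIF = λt/(λt+λd) × [1 − exp(−(λt+λd)·T)]

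**Worked case, S₅ = 22%, T = 5 years.** λd = −ln(0.22)/5 = 0.3028. 1-KM = 1 − exp(−0.25) = 22.1%. CIF = 0.05/0.3528 × [1 − exp(−1.764)] = 11.7%. Ratio 1.88.

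**All cited survival figures, λt = 5% per year**

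| S₅ | λd | CIF, 5 y (1-KM 22.1%) | Ratio | CIF, 2 y (1-KM 9.5%) | Ratio |
|---|---|---|---|---|---|
| 22% | 0.303 | 11.7% | 1.88 | 7.2% | 1.33 |
| 31% | 0.234 | 13.3% | 1.66 | 7.6% | 1.25 |
| 48% | 0.147 | 15.9% | 1.39 | 8.3% | 1.15 |
| 50% | 0.139 | 16.2% | 1.37 | 8.3% | 1.14 |
| 65% | 0.086 | 18.1% | 1.22 | 8.8% | 1.09 |

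**Level of the toxicity hazard.** Between 3% and 10% per year, the 5-year ratio runs from 1.91 to 1.83 at 22% survival, from 1.37 to 1.35 at 50%, and from 1.22 to 1.21 at 65%. The assumed level therefore matters little.

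**Shape of the hazards.** This matters more.
- Suppose toxicity can start only between 0.25 and 2 years, with 1-KM fixed at 20% and 22% survival. Then CIF is 14.5% counted from the end of radiotherapy (ratio 1.38), or 15.7% among patients alive at 3 months (ratio 1.28).
- With onset between 0.25 and 3 years, CIF is 12.8% (1.57) or 13.8% (1.45).
- With a constant toxicity hazard, 1-KM of 20% and 22% survival, a Weibull death hazard moves the 5-year ratio the other way if deaths come early: 2.33 at shape 0.6, against 1.76 at shape 1.2.

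The ratio exceeds 1 in every scenario.

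**The case against.** The strongest reply is that 1-KM answers a legitimate question: how toxic the treatment is, setting death aside. The cumulative incidence makes a treatment look safer when more patients die, so the choice is one of estimand. An overstated toxicity also cannot falsely reassure in a trial that aims to show acceptability. This stands in part, and it is why 1-KM may stay as a second, labelled figure. But the article announces the risk of developing late toxicity and does not say that a net risk is meant.

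It can also be said that censoring of deaths is nowhere written. That is true; it is inferred. With toxicity as the sole event, however, Kaplan-Meier leaves no other way to treat a toxicity-free death. The method is fixed in the text, so this is not a detail left to an analysis plan.

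The crude incidence, also to be recorded, is a partial safeguard. It does not replace a proper estimate, because with incomplete follow-up it tends to be too low.

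The size is open to challenge. At 2 years the gap is 9.5% against 7.2% to 8.8%, or about 1 to 2 points. The binomial 95% half-width around 7.2% with 76 patients is about 6 points (1.96 × √(0.072 × 0.928/76) = 0.058). This stands: at short horizons the bias is smaller than the sampling error.

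Three further inferences are tempting, and the article does not support them.
- A reader might infer that the late risk will be nearly doubled. That needs 22% survival, a 5-year horizon and a toxicity hazard that persists. Patients below pT3 can also enter, through nodal status, margins or a low node count.
- A reader might extend the point to the endpoint defined as "Bladder cancer specific survival calculated from date of radical cystectomy till death due to MIBC". Kaplan-Meier is a conventional net measure there, and the article gives no other-cause mortality from which to size any gap.
- A reader might infer that comparison with earlier trials is distorted. The article does not say how those trials estimated late toxicity.

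**Conclusion.** The point holds for late toxicity. 1-KM with death outside the event overstates the actual risk. Under constant hazards the overstatement at 5 years is about 1.2 fold at 65% survival, 1.4 fold at 48 to 50%, 1.7 fold at 31% and 1.9 fold at 22%. At 2 years it is about 1.1 to 1.3 fold. At 22% survival it is about 1.3 to 1.6 fold if onset is confined to the first 2 to 3 years.

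The direction is certain whenever patients die before toxicity could occur. The size depends on the survival actually seen in this cohort, on the reporting time, which the article does not fix, and on the shape of both hazards. The 5% per year is an assumption.

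The consequence is limited. Late toxicity is a secondary endpoint with no threshold attached, and neither the acute primary endpoint nor the sample size of 76 is affected. The change is still worth making, because the late figure bears on the trial's question of acceptability and the correction is nearly free.

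**What to change.** Replace the Kaplan-Meier sentence for late toxicity. Estimate the cumulative incidence of late toxicity by the Aalen-Johansen method, with time from the end of radiotherapy and death without late toxicity as a competing event, and report it with 95% confidence intervals. If 1-KM is also reported, label it a net risk, meaning toxicity in the absence of death. Leave the Kaplan-Meier plan for the survival endpoints as it is.

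The cost is one sentence in the analysis section and a standard software option. Dates of death are already needed for overall survival, so no new data, visits or patients are required.
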